## Abstract

**Background:** Primary indicated prevention in individuals at-risk for psychosis has the potential to improve the outcomes of this disorder. The ability to detect the majority of at-risk individuals is the main barrier toward extending benefits for the lives of many adolescents and young adults. Current detection strategies are highly inefficient. Only 5% (standalone specialized early detection services) to 12% (youth mental health services) of individuals who will develop a first psychotic disorder can be detected at the time of their at-risk stage. To overcome these challenges a pragmatic, clinically-based, individualized, transdiagnostic risk calculator has been developed to detect individuals at-risk of psychosis in secondary mental health care at scale. This calculator has been externally validated and has demonstrated good prognostic performance. However, it is not known whether it can be used in the real world clinical routine. For example, clinicians may not be willing to adhere to the recommendations made by the transdiagnostic risk calculator. Implementation studies are needed to address pragmatic challenges relating to the real world use of the transdiagnostic risk calculator. The aim of the current study is to provide *in-vitro* and *in-vivo* feasibility data to support the implementation of the transdiagnostic risk calculator in clinical routine.

**Method:** This is a study which comprises of two subsequent phases: an *in-vitro* phase of 1 month and an *in-vivo* phase of 11 months. The *in-vitro* phase aims at developing and integrating the transdiagnostic risk calculator in the local electronic health register (primary outcome). The *in-vivo* phase aims at addressing the clinicians' adherence to the recommendations made by the transdiagnostic risk calculator (primary outcome) and other secondary feasibility parameters that are necessary to estimate the resources needed for its implementation.

**Discussion:** This is the first implementation study for risk prediction models in individuals at-risk for psychosis. Ultimately, successful implementation is the true measure of a prediction model's utility. Therefore, the overall translational deliverable of the current study would be to extend the benefits of primary indicated prevention and improve outcomes of first episode psychosis. This may produce significant social benefits for many adolescents and young adults and their families.

## Introduction

Outcomes of psychotic disorders are associated with high personal, familial, societal, and clinical burden (1). There is thus an urgent clinical and societal need for improving outcomes of psychosis (1). The past two decades of clinical research have opened new opportunities for ameliorating outcomes of psychosis by intervening during its early clinical stages (1), in individuals at Clinical High Risk for psychosis [CHR-P (2)] -such as those meeting the At Risk Mental State criteria (3) or other similar criteria (4)-. This type of intervention is termed as “primary indicated prevention.” CHR-P individuals display subtle symptoms and overall functional impairment (5) that are due to the accumulation of several risk factors for psychosis (6, 7). In the wake of these issues (8), they seek help at specialized CHR-P clinics (9), where they receive a comprehensive psychometric assessment in the context of a clinical interview (10). Overall, the prognostic performance of this assessment is considered to be good [except for their use as screening tools in the general population (11, 12)] and comparable to that of similar prognostic measurements that are employed in organic medicine (13). Under those circumstances, CHR-P individuals have a 20% [see eTable 4 in (14)] probability of developing emerging psychotic disorders [but not other non-psychotic disorders (15, 16)] over a relatively short period of 2 years. Primary indicated prevention in CHR-P individuals has the unique potential to alter the course of psychosis and reduce the duration of untreated psychosis, although there is some uncertainty with respect to the true effectiveness of available treatments (17–21). An additional potential advantage is that secondary prevention in CHR-P who will develop the disorder can reduce the duration of untreated psychosis and ameliorate the severity of the disorder (1, 22). As summarized in Figure 1, the potential real world impact of the CHR-P paradigm for improving the outcomes of psychotic disorders is determined by the successful and stepped integration of the following key components:

Efficient detection of individuals at-risk for psychosis;Accurate prognosis of outcomes;Effective preventive treatment.

**Figure 1 F1:**
[figure not shown]
Core clinical and research components for effective prevention of psychosis.

illustrated in Figure 1, the first rate-limiting step for improving outcomes of psychosis through the CHR-P paradigm is the detection of individuals who are at risk for psychosis. In fact, even the most accurate prognostic tool and the most effective preventive treatment would have little impact on improving the outcomes of psychosis without proper scalability to the vast majority of the at-risk population. Our lab (the Early Psychosis: Intervention and Clinical-detection, EPIC) has investigated the effectiveness of current detection strategies for identifying CHR-P individuals for the first time. These strategies are largely based on referrals to specialized CHR-P clinics (9) that are made on suspicion of psychosis-risk (23). Our local National Health Service (NHS) Trust, The South London And the Maudsley (SLaM), in partnership with King's College London and King's Health Partners, hosts one of the largest clinical services for CHR-P individuals worldwide: the Outreach And Support In South London (OASIS) (24). Established in 2001, the OASIS has emerged as a reference point for psychosis prevention in the UK and worldwide (24). The OASIS is detecting CHR-P individuals from the community, primary care, and secondary care through an extensive and ongoing outreach campaign, which has been fully established over the past years. Despite this outreach, we have found that OASIS' detection strategies are highly inefficient because only 5% of individuals diagnosed with a first episode of non-organic ICD-10 psychosis in SLaM had been detected at their CHR-P stage. This finding has clear-cut clinical implications. For example, NHS England, in April 2016 has implemented a new Access and Waiting Times-Standard for Early Intervention in psychosis, which requires that CHR-P are detected nationwide and treated rapidly (25, 26). Although it is now an NHS requirement that all suspected CHR-P patients who present to NHS Trusts are assessed and interviewed for a psychosis-risk state (13), such an approach is likely to miss the vast majority of those at risk. No alternatives are on the horizon. Intensifying the inefficient outreach campaigns currently adopted by CHR-P clinics is not viable because these campaigns are idiosyncratic and unstandardized (23, 27, 28), leading to a diluted transition risk and unreliable prognosis (11, 12). Front-line youth mental health services such as the Headspace initiative -as opposed to specialized CHR-P clinics such as the OASIS- are also expected to detect more at-risk individuals. Unfortunately, even youth mental health services can detect only 12% of first episode cases at the time of their CHR-P stage (29). It is thus clear that to extend the benefits of the CHR-P paradigm some innovative approaches are urgently needed (30).

To overcome these issues, we have developed a pragmatic, clinically-based, individualized, transdiagnostic risk calculator for the detection of individuals at risk of psychosis in secondary mental health care at scale (24). In a subsequent step, the calculator has been externally validated, demonstrating good prognostic accuracy (24). Yet, a good model's (external) performance is necessary but not sufficient to ensure a clinical use of a risk calculator. Implementation studies are first needed to address pragmatic challenges relating to the use of a risk calculator in clinical routine (31). These challenges may suggest adaptations to the original models to allow its usability in the real world. Ultimately, successful implementation is the true measure of a prediction model's utility (32). For example, the transdiagnostic risk calculator was developed on retrospective cohort data (24). As such, it is not known whether it can be used prospectively in the real world of NHS Trusts. Data that are necessary to run the calculator (age, gender, age by gender, ethnicity, and ICD-10 index diagnosis) may not be available or not accessible. Furthermore, clinicians' adherence to the recommendations made by the transdiagnostic risk calculator is unknown. This represents the critical barrier toward its scalability in clinical routine. We describe here the protocol for the implementation study of this transdiagnostic risk calculator in the NHS. To our best knowledge, this will be the first implementation study of a risk calculator for clinical routine in the CHR-P field.

The overall translational deliverable of the current study would be to extend the benefits of primary indicated prevention and improve outcomes of first episode psychosis. This, in turn, may produce significant social benefits and cost-saving to many adolescents and young adults, their families and the NHS.

## Methods

This is a feasibility study which will evaluate essential real world parameters associated with the implementation of an electronic, clinically-based, individualized, transdiagnostic risk calculator for the detection of individuals at risk and the prediction of psychosis in secondary mental health care. Obtaining these figures is a necessary step in order to accurately estimate the resources (e.g., staffing) needed for the routine clinical use of the calculator. There are two phases in this study: an initial *in-vitro* (1 month) testing which does not involve patients contact and a second *in-vivo* piloting (11 months, total study duration 12 months), which involves recruitment of SLaM patients. Before we present the study design, we will briefly summarize the core characteristics of the transdiagnostic risk calculator.

### Clinically-Based, Individualized, Transdiagnostic Risk Calculator for the Automatic Detection of Individuals at Risk of Psychosis in Secondary Mental Health Care

In a previous meta-analysis, we showed that secondary mental health care is the most frequent source of referrals to CHR-P services such as the OASIS (23). We additionally confirmed that the recruitment of individuals for CHR-P assessment through secondary mental health services is associated with the highest probability of developing psychosis (27). In fact, these individuals are more likely to have accumulated several risk factors for psychosis such as affective comorbidities, substance abuse and social deprivation (6). These findings are concurrent to the European Psychiatric Association guidelines, which recommend that CHR-P assessment should only be offered to individuals who are “already distressed by mental problems and seeking help for them” (33). The transdiagnostic risk calculator presented here is therefore in line with the clinical guidelines in the field.

Our calculator was developed and externally validated in a large clinical dataset of non-psychotic patients affected with non-organic mental disorders (*n* = 91,199), in the National Institute of Health Research (NIHR) Maudsley Biomedical Research Centre (BRC) Case Register. This register is electronic, because SLaM is paper-free, and all clinicians record their activity electronically on the Patient Journey System (PJS), as part of their clinical routine. PJS is a comprehensive record of all clinical information recorded throughout patients' journeys through SLaM NHS Trust services, including demographic and contact information, dates and other details of referrals and transfers, detailed clinical assessments, care plans and medication, clinical activity, and reviews. Anonymised information from PJS is subsequently used to create the Clinical Record Interactive Search (CRIS). CRIS allows researchers to search from PJS records. The details of the CRIS and the local electronic health record have been published previously (34–36). Therefore, this calculator leverages the potentials of e-Health innovations. The original study followed state-of-the-art guidelines for model development and validation (37). Thus, the external validation was done through a geographical split of the initial database in a derivation (Lambeth and Southwark SLaM boroughs, *n* = 33,820) and validation (Lewisham and Croydon SLaM boroughs, *n* = 54,716). The calculator showed good prognostic accuracy in the external validation, in terms of overall performance (*R*^2^ = 0.72), discrimination (Harrell's C = 0.79) and calibration (calibration slope = 0.96) (24). Our calculator is based on simple sociodemographic variables (age, gender, ethnicity, age by gender interaction and ICD-10 index diagnosis) that can be easily accessed in clinical practice. It has been termed as “transdiagnostic” because it leverages several ICD-10 index diagnoses, and it can detect risk of psychosis across all diagnostic spectra (i.e., acute and transient psychotic disorders, substance abuse disorders, bipolar mood disorders, non-bipolar mood disorders, anxiety disorders, personality disorders, developmental disorders, childhood/adolescence onset disorders, physiological syndromes and mental retardation). This also represents one of the broadest transdiagnostic studies in psychiatry overall (38). The selection of predictors that were available in the local electronic health records was deliberately done with the view of facilitating its implementation in clinical routine at scale, which is an essential prerequisite to improve the detection of individuals at risk of psychosis. The predictors were preselected on the basis of a priori meta-analytical knowledge (39), a method which is recommended to develop robust prognostic models (31). In fact, the calculator is characterized by a significant clinical utility (net benefits) within a 1–50% range of threshold probability (individuals risk of developing psychosis by 5 years) (24). Such a range of predicted risk for psychosis is clinically meaningful since it is unlikely that a calculator would be needed to guide clinical practice for individuals with higher or lower predicted risks. The transdiagnostic risk calculator has also been implemented online (www.psychosis-risk.net) (24). This would allow its use in NHS Trusts that do not routinely employ electronic health records. An example of the output that is provided by the transdiagnostic risk calculator is appended in Figure 2. The core characteristics of the transdiagnostic risk calculator are appended in Table 1.

**Figure 2 F2:**
[figure not shown]
Example of outcomes produced by the transdiagnostic risk calculator that is under implementation in the current study.

**Table 1 T1:** Core characteristics of the transdiagnostic risk calculator.

Robust	It includes predictors that have been selected through a priori clinical knowledge
Pragmatic	It is agnostic with respect to etiopathology of psychosis
Cheap	It leverages predictors that are routinely collected by clinicians
Automatized	It can accommodate electronic health records as well as the manual entry of predictors
e-Health	It has been implemented online
Scalable	It can be used to screen large electronic health records
Optimisable	It can be further refined by the inclusion of other predictors

### Design

#### *In-vitro* Phase

The initial phase will have the transdiagnostic risk calculator integrated into the local electronic health register (step 0, Figure 3). This will involve several activities such as developing the prototype, addressing *in-vitro* feasibility problems associated with its implementation in SLaM clinical practice, and conducting clinician engagement work prior to initiating the *in-vivo* piloting. The team has already started initial work to prepare the implementation of the calculator. Firstly, we have approached the local NHS Trust IT facility (SL@M Connect) to discuss governance issues for using clinical material from the local NHS Trust. SL@M Connect has endorsed our study and will support it. Secondly, we have conducted data quality checks with the CRIS team to ensure that the resources needed are in place. Thirdly we have started the *in-vitro* phase by extracting preliminary data and running our calculator. We have also collaborated with the Center for Translational Informatics in order to fully implement the calculator in the local electronic health register. Anonymised data will be used during this phase to develop a prototype of the tool that can be automatised within the local electronic health register. Qualitative data will be collected to identify pragmatic barriers associated with the use of the transdiagnostic risk calculator. This will be collected through organizing two workshops, each composed of five SLaM clinicians. This phase would also tune the pilot threshold probability to be used in the next phase and address implementation challenges that have emerged from the *in-vitro* phase. This phase will be developed in collaboration with SLaM IT Connect and with the Center for Translational Informatics at the Institute of Psychiatry, Psychology, and Neuroscience. Approval for the *in-vitro* study was granted by the Oxfordshire Research Ethics Committee C. Because the data set is made up of de-identified data, informed consent is not required. Furthermore, during this phase we will try to complete a further external validation of the transdiagnostic risk calculator in an independent NHS Trust in the UK which is using CRIS. This is seen as an essential step to address the transportability of our transdiagnostic risk calculator across different clinical scenarios.

**Figure 3 F3:**
[figure not shown]
Flow chart of study design including the *in-vitro* and *in-vivo* phase.

The *in-vitro* phase will last 1 month.

### *In-vivo* Phase

This phase will consist of a prospective feasibility study to test the real world usability of the transdiagnostic risk calculator to detect individuals at risk of psychosis at scale in clinical routine.

During this phase, a prototype will be made freely available to clinicians working in secondary mental health teams. In practice, clinicians will not be required to enter any new variables because all the predictors are already available as part of the standard clinical practice. In the first step (see step 1, Flow chart), the research team will screen potential patients meeting our study criteria using de-anonymised electronic health register data (CRIS). The data for these patients will be accessed by the study team to screen potential participants with the transdiagnostic risk calculator. The electronic health register will also be used to identify the responsible clinician for any individuals who are at risk as determined by the pre-defined threshold (established during the *in-vitro* phase).

The research team will then contact the responsible clinician through manual alerts (e.g., emails) and phone contact, recommending the patient be referred for a refined psychosis assessment. If an individual does not reach the threshold, the calculator will recommend no further assessment and standard care will be offered as usual. If possible, these alerts will be automatised during the study. During the second step (step 2, Flow Chart), the responsible clinicians will then decide whether to initiate the referral or not. A crucial outcome to be investigated will be the impact of different types of alerts on the clinicians' adherence on the use of the transdiagnostic risk calculator. If the individual is not referred for further assessment, standard care will be offered as usual. In the case the participant is referred for further assessment, the clinician will ask the patient if they consent to their details being given to the research team. If they do, the individual will be contacted by the research team and the procedure for collecting informed consent will be initiated.

If the patient agrees to participate in the study, they will then be invited to undergo a refined assessment (step 3, Flow Chart), which includes the standard CHR-P assessment. Specifically, we will use the combined Comprehensive Assessment for At Risk Mental States (CAARMS, version 12/2006) (3) and Structured Interview for Prodromal-Risk Syndromes, version 5.0 (SIPS) (40), clinician-rated and iPad version, that have been developed in our department as part of previous ongoing studies.

At the end of this assessment, the researchers would communicate the results to the responsible clinicians (step 4, Flow Chart). In case the individuals would meet the standard intake criteria for a state of risk for psychosis (i.e., a CHR-P state), they would be referred to the local Clinical High Risk service [the OASIS (9)] for standard care as recommended by the NICE (41). If the individuals do not meet the intake criteria for a CHR-P state, the referrer will be informed, and standard care provided accordingly. Overall, there will be no change in the current standard care for any participants. This prototype will be piloted in all local secondary mental health services present in the borough of Lambeth, Lewisham, Croydon and Southwark.

Participants will be reimbursed for their participation in the study at an hourly rate of £10. For patients under the age of 16, their time will be reimbursed with Amazon gift vouchers, again to the value of an hourly rate of £10 per hour. Table 2 lists the study procedures.

**Table 2 T2:** Study procedures for individuals detected by the transdiagnostic risk calculator and referred by clinicians for an assessment for psychosis-risk.

		**Baseline**		**Follow-up**
	**Screening Visit**	**Day 1**	**Day 2 (2 weeks+- 3 days)**	**6 months +- 2 weeks**
Patient information and informed consent	**X**			
CHR-P assessment		**X**	**X**	**X**

*The in-vivo phase will last 11 months*.

### Follow-Up

Individuals who are selected through the transdiagnostic risk calculator, referred by their clinicians for a psychosis-risk assessment and who accept it will be invited again to a face-to-face clinical follow-up at 6 months. This will consist of the same measures acquired at baseline.

### Statistics

#### Sample Size

This is a feasibility study to investigate key implementation parameters for an electronic risk calculator. As such the study is neither designed nor powered to validate new tools or test specific hypotheses.

The primary outcome of the *in-vitro* phase is the development and integration of the transdiagnostic risk calculator in the local electronic health register. As such, no power calculation is made for the *in-vitro* primary outcome.

They key rate-limiting barrier toward a scalable use of the transdiagnostic risk calculator in the broader clinical scenario is the clinicians' adherence to the recommendations made by the calculator itself. Therefore, the primary outcome of the *in-vivo* phase of this study is the adherence of clinicians to the use of the calculator, defined by the proportion of clinicians who have responded to the prompts sent on the recommendation of the electronic risk calculator from SLaM secondary mental health care. The sample size calculation is therefore made for this primary outcome. In line with the NIHR guidance, our main outcomes are feasibility parameters, and sample size calculation is made for the expected level of precision (45). Assuming a predicted psychosis threshold of 5–10% (at 2 years), on the basis of the previous study (24), we expect to detect at least 120 at-risk individuals per 11 months recruitment in SLaM. Conservatively assuming that only half of SLaM clinicians would eventually respond to the alerts generated by the calculator, the anticipated sample size would allow us to have an acceptable (42) maximum margin of error of 0.1 (i.e., 95%confidence interval (CI) ±0.1) for adherence rates of clinicians >60%. The secondary outcomes of the *in-vivo* phase will measure other key feasibility parameters that are necessary to implement the calculator in the wider clinical routine: impact of different types of alerts on the clinicians' adherence to the recommendations made by the transdiagnostic risk calculator; raw number of referrals initiated from secondary mental health care clinicians for an assessment of psychosis-risk; qualitative reasons for any lack of clinicians' adherence.

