#### Analysis

This is a feasibility study and it is not planned to test any statistical hypotheses with regard to any of the endpoints in a confirmatory sense. For the exploratory evaluation of our hypotheses, a two-sided 95% CI of adjusted treatment differences will be computed. However, the CIs will have to be interpreted in the perspective of the exploratory character of study, i.e., as an interval estimate for effects under these conditions. All statistical analyses will be performed using STATA version 14 (43).

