#### *In-vivo* Phase

Primary outcome: adherence of clinicians to the use of the transdiagnostic risk calculator (proportion of clinicians who have responded to the prompts sent on the recommendation of the transdiagnostic risk calculator).Secondary outcome: impact of different types of alerts on the clinicians' adherence to the recommendations made by the transdiagnostic risk calculator.Secondary outcome: raw number of referrals initiated from secondary mental health care clinicians for an assessment of psychosis-risk.Secondary outcome: qualitative reasons for any lack of clinicians' adherence.

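### The ±0.1 precision for clinician adherence is not demonstrated: the calculation counts flagged patients, the outcome counts clinicians, and the 50% assumption and the >60% condition do not fit together

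*Protocol article*

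**What the plan says.** The Sample Size section makes clinician adherence the in-vivo primary outcome, "defined by the proportion of clinicians who have responded to the prompts sent on the recommendation of the electronic risk calculator". The outcomes list repeats this: "proportion of clinicians who have responded to the prompts sent on the recommendation of the transdiagnostic risk calculator". In both places the unit is the clinician.

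The Sample Size section says its calculation is made for this outcome and aims at precision. It has three ingredients:

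- a count: "we expect to detect at least 120 at-risk individuals per 11 months recruitment in SLaM";
- a planning value: "Conservatively assuming that only half of SLaM clinicians would eventually respond to the alerts generated by the calculator";
- a result: a "maximum margin of error of 0.1 (i.e., 95%confidence interval (CI) ±0.1) for adherence rates of clinicians >60" per cent.

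The design description of the in-vivo phase says who receives an alert: "The research team will then contact the responsible clinician through manual alerts (e.g., emails) and phone contact". An alert thus follows from a flagged patient and goes to that patient's clinician. Nothing says that each flagged patient has a different clinician.

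**The concern.** Two things in the precision statement do not fit the outcome it is meant to support.

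The first is the unit. The count is of patients and the outcome is a proportion of clinicians. If any clinician is responsible for more than one flagged patient, there are fewer clinicians than patients. The half-width depends on the number of clinicians, which the article does not give.

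The second is the planning value. The outcome is itself the response proportion, so assuming that half respond puts it at 50%. The margin is claimed only above 60%, so the case called conservative falls outside the claim. If the half is instead meant to shrink the sample from 120 to 60, the margin comes out larger than stated over most of the range.

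This is the only quantitative justification for the in-vivo primary outcome, in a study that says its sample size is set for precision.

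**Working it through.** **Inputs.** From Sample Size: at least 120 flagged patients, assumed response 0.50, claimed 95% half-width 0.1, claimed range above 60%. From the design description: one alert per flagged patient, sent to the responsible clinician. The number of clinicians, patients per clinician and intraclass correlation (ICC) are not given, so they appear below only as labelled assumptions.

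**Formula.** Half-width for a single proportion: h = 1.96 × √(p(1 − p)/n). Solved for n: n = 1.96² × p(1 − p)/h².

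**Step 1: try to reproduce the plan's figure.**

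- 120 independent units: at p = 0.5, h = 1.96 × √(0.25/120) = 0.0895; at p = 0.6, h = 1.96 × √(0.24/120) = 0.0877. The value at 0.5 is the largest possible, so ±0.1 holds at every rate and the 60% condition does no work. The exact (Clopper–Pearson) interval agrees: its longer arm is 0.0926 at 50% and 0.0934 at 60%.
- 60 units (half of 120): h = 0.1265 at 50%, 0.1240 at 60%, 0.1160 at 70% and 0.1012 at 80%. Setting h = 0.1 gives p(1 − p) = 0.01 × 60/1.96² = 0.156, so p = 0.806. The cut-off would be about 81%, not 60%.
- n that would make 60% the cut-off: 1.96² × 0.24/0.01 = 92.2, so 93. This is neither 120 nor 60.

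With 120 units, 0.1 is true as a loose upper bound. Neither reading produces a boundary at 60%.

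**Step 2: clinicians needed for ±0.1.** At 50%: 1.96² × 0.25/0.01 = 96.04, so 97. At 60%: 93. With 120 patients this allows on average 120/97 = 1.24 patients per clinician at 50%, or 120/93 = 1.29 at 60%. These are normal-approximation figures; with the exact interval 97 clinicians at 50% give a longer arm of 0.1034, so slightly more would be needed.

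**Step 3: half-width on the correct unit.** Patients per clinician is assumed, with 120 patients.

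| Patients per clinician | Clinicians | h at 50% | h at 60% |
|---|---|---|---|
| 1.0 | 120 | 0.0895 | 0.0877 |
| 1.2 | 100 | 0.0980 | 0.0960 |
| 1.5 | 80 | 0.1096 | 0.1074 |
| 2 | 60 | 0.1265 | 0.1240 |
| 3 | 40 | 0.1549 | 0.1518 |

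**Step 4: the alternative unit.** If adherence were counted per alert, 120 alerts would be the denominator, but alerts to one clinician are correlated. Design effect = 1 + (m − 1) × ICC, with m alerts per clinician; the effective n is 120 divided by it. At 50%, for an assumed ICC of 0.2 to 0.5:

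- m = 2: design effect 1.2 to 1.5, effective n 100 to 80, h = 0.098 to 0.110.
- m = 3: design effect 1.4 to 2.0, effective n 85.7 to 60, h = 0.1059 to 0.1265.

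**The case against.** The strongest reply is that the sentence is not false. It gives a maximum margin, and with 120 independent units the half-width above 60% is at most 0.0877. On that reading the 60% condition is superfluous, and its conflict with the 50% planning value has no numerical effect, since 50% gives 0.0895. This stands.

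A reader might go further and infer that the margin will not be met. The article does not support that. The pilot is described as covering all local secondary services in four boroughs, and if the flagged patients belong to at least 97 clinicians, ±0.1 is met at any rate. Nor is 120 a ceiling: it is stated as a minimum. Equally, nothing in the article shows that 97 clinicians will be involved, and the inclusion criteria name Lambeth alone.

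A reader might also infer that the outcome rises mechanically with the number of prompts per clinician. That presumes that one reply to any prompt counts as a response, which the article does not say.

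A further reply is that a journal article condenses a fuller protocol, where the clinician count may stand. That would excuse a bare omission. It does not remove the mismatch and the inconsistency in what the article itself prints.

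Finally, the study is exploratory, tests no confirmatory hypothesis and sets no success threshold. An interval computed on the observed number of clinicians will show the precision achieved. This stands and limits the seriousness of the point.

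**Conclusion.** The point holds in this form: ±0.1 is not demonstrated for the primary outcome as defined. The calculation uses patients where the outcome uses clinicians, the planning value of 50% lies outside the range claimed, and the 60% cut-off follows from no stated input.

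The size depends on a number the article does not give. With 97 or more distinct clinicians the margin is met at 50%. With an assumed 80, 60 or 40 it is 0.1096, 0.1265 or 0.1549. These figures assume independent clinicians and the normal approximation.

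This should be corrected, but it is not critical. It does not bias the estimate, and no decision depends on the margin.

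**What to change.** Keep the clinician as the unit. In Sample Size, state the expected number of distinct responsible clinicians and restate the 95% half-width on that number at the assumed 50%. If the number is uncertain, give the range from step 3: 120 clinicians about ±0.09, 80 about ±0.11, 60 about ±0.13, 40 about ±0.155. Delete the 60% condition, or say which n it comes from and reconcile it with the 50% assumption.

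Reporting adherence per alert is an option, not a required correction. It can be a supporting analysis. As the primary outcome it would be an amendment, since in-vivo recruitment began on 1 August 2018 and the ethics section requires a favourable opinion before a substantial amendment is implemented. Either way, use a 95% interval clustered by responsible clinician and state the assumed ICC with the resulting margin (step 4).

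Cost: a change of wording and a stated margin that may be slightly less favourable than ±0.1. No extra patients are needed.
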